#### 5.2.1.1 Sensitivity analysis

Three types of rates will be calculated:

- 1) Outcomes identified by sites pre-amendment
- 2) Outcomes identified by sites post-amendment
- 3) Outcomes based on additional information collected and interpreted at the backend (preterm birth based on data point GA, low birth weight based on data point birth weight, SGA based on data points sex and GA (and interpreted using chart), congenital microcephaly based on sex, GA and head circumference (and interpreted using chart; only for sites at which head circumference is routinely collected).

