| 2.0            | 30Nov18             | Clarify the timelines for data collection.
Change in information recorded on deliveries.
Update the CRFs accordingly                                                                                                               |
| 2.1            | 26 June 2019        | Correction of one of the two satellite sites in Spain                                                                                                                                                                                    |
| 3.0            | 1 Nov2019           | Collection of 4 additional data points to obtain reliable count of outcomes of interest
Simplify the recruitment rules of study participants
Update information on participating sites, scientific committee members and timelines |

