#### 4.7 Case identification and vaccine exposure assessment

Identified cases are defined as children delivered at the site with a diagnosis of one of the health outcomes of interest at the same site. A list of potential cases will be drawn on a regular basis (e.g. weekly) from relevant data sources (see section 3.7).

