## 4.9 Data collection

Each delivery that takes place at the site will be registered and the occurrence of any outcomes of interest within 28 days of birth will be recorded in the electronic data capture system (EDC). In addition, the sex, birth weight, gestational age and the head circumference will be collected. From this, the total number of live births over one year and the total number of cases identified among those delivered at the site will be derived.

Once an outcome occurs and the inclusion and exclusion criteria are met (including informed consent), the infant enters the study. At each site, cases with outcomes of interest will be consecutively recruited into the study, until 100 cases for each outcome have been recruited, or the end of the study period is reached, whichever occurs first.

One infant may present with more than one outcome under study; cases will be recruited for all outcomes until 100 cases for each outcome has been reached. . Data on case ascertainment for each case and maternal vaccination status of the case's mother will be collected in an electronic CRF in an electronic data capture (EDC) system. CRFs are available in Annex 5. If necessary, a paper CRF may be used as an intermediary step.

The EDC system will generate a unique ID for each child. Forms for child and mother shall be automatically linked to this unique ID where appropriate. Country and site codes shall also be assigned by the data management centre.

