#### 4.10 Case classification

Identified cases and exposures will be classified using the Brighton Collaboration ABC tool (Automatic Brighton Classification) [20] according to the levels of diagnostic certainty present in the GAIA definitions (Level 1-3, and Level 4-5 when applicable).

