## 5.2 Data analysis: Primary study outcomes

### 5.2.1 Primary study outcome 1 – Minimum detectable risk

The minimum detectable risk that can be detected for each health outcome in a future study will be quantified for each GAIA case definition. The minimum detectable risk will be the minimum detectable odds ratio (OR) in a case-control study design and the minimum detectable relative risk (RR) in a cohort study design. This information will be useful to establish the sample size that can be achieved in a one-year period for a specific health outcome in future studies, and the minimum detectable risk that could be achieved. Note that the data collected on maternal vaccination during the study will not be used in this calculation, as this data were collected solely to assess the applicability, and not to assess risk associated with maternal vaccinations currently in use.

For the case-control study design, the minimum detectable OR for each health outcome will be calculated based on:

- Number of cases classified during the study period,
- Different theoretical levels of exposure (maternal vaccination) among cases and controls,
- The ratio of cases to controls,
- 80% power and 95% confidence level,
- Per year of study duration.

For the cohort study design, the minimum detectable RR for each health outcome will be calculated based on:

- Different theoretical percentages of exposed (maternal vaccination) and non-exposed (no maternal vaccination) with each health outcome,
- Different theoretical levels of exposed to unexposed ratio,
- 80% power and 95% confidence level,
- Per year of study duration

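### The minimum detectable OR rests on site-diagnosed, consented cases capped at 100 per outcome and site, and leaves out the register values added to count outcomes reliably

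*Protocol*

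**What the plan says.** The version history gives the purpose of version 3.0 as "Collection of 4 additional data points to obtain reliable count of outcomes of interest". Sections 4.6 and 4.9 show the fields now recorded for every delivery: sex, birth weight, gestational age and head circumference.

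For the case-control design, section 5.2.1 lists as its count "Number of cases classified during the study period". A footnote in the protocol explains that classified means classified to the GAIA definition. Section 4.10 states what is classified: "Identified cases and exposures will be classified using the Brighton Collaboration ABC tool". Section 4.7 states who is identified: "Identified cases are defined as children delivered at the site with a diagnosis of one of the health outcomes of interest at the same site". Sections 4.3 and 4.9 add maternal consent and consecutive recruitment that stops at 100 cases per outcome per site.

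Section 5.2.1.1, headed as a sensitivity analysis, lists three rates: site-identified before the amendment, "Outcomes identified by sites post-amendment", and "Outcomes based on additional information collected and interpreted at the backend". The third covers preterm birth, low birth weight, SGA and, where head circumference is routinely collected, congenital microcephaly.

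For the cohort design, section 5.2.1 names no observed count. Its input is "Different theoretical percentages of exposed (maternal vaccination) and non-exposed (no maternal vaccination) with each health outcome".

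**The concern.** Section 5.2.1 says the result should show what sample size a one-year study could reach and what risk it could detect. That calls for the fullest defensible yearly count.

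Low birth weight, preterm birth and SGA are threshold rules on recorded values (sections 4.7.2, 4.7.5 and 4.7.6). An infant recorded below 2500 g meets the threshold whether or not anyone wrote the diagnosis down. Sites find cases by manual review, free-text search or ICD codes, in sources that differ between sites (section 4.8). Labelled cases can therefore fall short of the cases present in the register.

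The cap acts in the same direction. It was set to give adequate precision for the applicability proportions, which are the second primary outcome. It was not set for the minimum detectable risk, yet it limits how many cases have a completed CRF and so can be classified. If either mechanism operates, a future study at that site looks less capable than it would be.

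**Working it through.** **1. The plan's own figure.** The only sample-size calculation is Table 1 in section 5.1.2, which belongs to applicability. With n = 1.96² × p(1 − p)/d², p = 0.50 and d = 0.10, n = 3.8415 × 0.25/0.01 = 96.04, rounded up to 97. This agrees with the protocol and is the origin of the 100-case target. The protocol states no figure for minimum detectable risk.

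**2. What feeds the OR.** The path is: site diagnosis (4.7), consent (4.3), recruitment up to 100 (4.9), completed CRF, GAIA classification (4.10), number classified (5.2.1). The register values are not named at any step. Section 5.1.1 says that all identified cases are included, which conflicts with the cap in 4.3, 4.9 and 5.1.2. The text does not say how cases beyond the cap would be classified without a CRF.

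**3. Effect of a lower count.** Inputs from 5.2.1: 80% power and 95% confidence, taken as two-sided 5%. Assumed, because the protocol leaves them open: case numbers, r = 4 controls per case, and exposure among controls p0 of 10% or 30%.

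Formulas:
- p1 = OR·p0 / [1 + p0(OR − 1)]
- p̄ = (p1 + r·p0)/(1 + r)
- cases = {1.96·√[(1 + 1/r)·p̄(1 − p̄)] + 0.8416·√[p1(1 − p1) + p0(1 − p0)/r]}² / (p1 − p0)²

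For OR = 1.39 and p0 = 0.30: p1 = 0.417/1.117 = 0.3733 and p̄ = 0.3147. The numerator root is 1.0176 + 0.4504 = 1.4680. Then (1.4680/0.0733)² is about 400.

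For OR = 1.90: p1 = 0.570/1.270 = 0.4488 and p̄ = 0.3298. The root is 1.0302 + 0.4609 = 1.4911. Then (1.4911/0.1488)² is about 100.

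| Cases | OR, 30% exposed | OR, 10% exposed |
|---|---|---|
| 400 | 1.39 | 1.60 |
| 360 | 1.41 | 1.63 |
| 200 | 1.59 | 1.89 |
| 100 | 1.90 | 2.36 |

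With 1 control per case and 30% exposed, halving 200 cases to 100 moves the OR from 1.79 to 2.27. Halving 1000 to 500 moves it from 1.31 to 1.45.

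**4. Missed cases or the cap.** With 400 true cases at a site, 90% labelling and no cap, 360 remain and the OR moves only from 1.39 to 1.41. If the cap applies, at most 100 are classified and the OR is at least 1.90, whether sites label half or all of the 400. At a high-volume site the cap can matter more than missed diagnoses.

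**5. The SGA rule.** Section 4.7.6 defines SGA by birth weight for gestational age. The SGA derivation in 5.2.1.1 names sex and gestational age only, so it cannot be computed as written. Birth weight is in the register, so this is an omission from the text and not a gap in the data.

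**6. Period covered.** Version 3.0 is dated 1 November 2019. On the tentative window in 4.4 (to 31 January 2020), at most 3 of 12 months follow it, a scaling factor of 12/3 = 4. If a 12-month window starts in May 2019 (section 10), 6 months follow, a factor of 2. Both assume immediate implementation and no back-filling, on which the protocol is silent.

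**The case against.** The strongest counter-argument is that 5.2.1 targets the risk detectable under each GAIA definition. A register value below a threshold is not a GAIA-classified case. Annex III requires dating evidence for preterm birth, weighing time and scale details for low birth weight, and both for SGA. The register holds none of these. This stands: replacing classified cases with the raw derived count would change the quantity being estimated. Multiplying the derived count by the classifiable proportion meets the objection.

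The derived count can also err upward. The general form in Annex V asks for 0 when birth weight is unknown. If the register follows that convention, a plain threshold rule would count those infants as low birth weight. This stands too.

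The text is also less definite about a hierarchy than it first appears. Both site-identified rates sit under the same sensitivity heading. In section 4.9, "the total number of cases identified among those delivered at the site will be derived" follows directly after the added fields, so it may already draw on them. Even so, the OR is specified on classified cases, and classification is described only for identified cases.

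A reader might infer that the whole minimum detectable risk runs on an under-ascertained count. The documents do not support that. The cohort relative risk is specified on theoretical percentages. Neonatal death, neonatal infection and stillbirth have no derived count. Under-identification is suggested by the amendment's purpose but is nowhere shown or sized. The underestimation admitted in section 6 concerns infants who seek no care or seek it elsewhere. Nor does the protocol plan to rank sites, or to interpret the difference between the pre- and post-amendment rates.

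**Conclusion.** The point holds for the minimum detectable OR and for four of the seven outcomes. The values added to make the count reliable do not enter the OR, and the count that does enter is limited by site diagnosis, consent and a cap chosen for another objective. The direction is certain: fewer cases give a larger minimum detectable OR.

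The size is illustrative. In the 4:1, 30% exposure example, halving 400 cases costs 0.20 on the OR (1.39 to 1.59), and falling to the cap costs 0.51 (1.39 to 1.90). At sites with fewer than 100 cases and near-complete labelling the effect is small. These figures rest on assumed case numbers, exposure and control ratio. The protocol does not allow the actual under-count to be computed.

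Separately, and without any assumption, the SGA derivation in 5.2.1.1 is incomplete as written.

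**What to change.** In 5.2.1, for low birth weight, preterm birth, SGA and (only where head circumference is routine) microcephaly, calculate the OR from:

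yearly cases = backend-derived count scaled to 12 months × proportion of CRF-completed cases classifiable under GAIA (the proportion already defined in 5.2.2.1).

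For example, 400 derived cases and an assumed 90% classifiable give 360 cases and an OR of 1.41 (4:1, 30% exposed). Capped recruitment with the same proportion gives 100 × 0.90 = 90 cases and an OR of 1.97.

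Also:
- State the delivery period that the derived count covers and the scaling rule.
- Treat a birth weight entered as 0 as missing.
- Report the OR from site-identified cases as the sensitivity analysis.
- Compare site-identified with derived counts only on the same post-amendment deliveries.
- Correct the SGA derivation to birth weight, sex and gestational age.
- Reconcile 5.1.1 with the cap in 4.3, 4.9 and 5.1.2.

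The cost is analysis wording; no new data are needed. There are two downsides. The derived count covers only part of the year, so scaling may carry some seasonal error. The product also assumes that unlabelled infants are as classifiable as those with a completed CRF, which should be stated.

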## 5.2.2 Primary study outcome 2: Applicability of GAIA case definition

### 5.2.2.1 Health outcomes

For each health outcome, applicability of GAIA case definition will be assessed by calculating the proportion of cases identified that can be classified according to the GAIA case definition.

The denominator will be the number of cases identified for which the CRF was completed for one health outcome; the numerator will be the number of cases identified for that health outcome that can be classified according to the GAIA case definition.

The applicability of the GAIA case definitions for each health outcome will be reported overall, and stratified by site/country/region, and by health facility level (primary/secondary/tertiary).

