## 4 Methodology

### 4.1 Study design

This will be a prospective observational study at selected sentinel sites, mostly in LMICs.

As this study is observational, no changes to routine clinical and diagnostic practice will take place, however data recording from routine clinical practice is expected to be more complete and data access easier than in a retrospective study. During a feasibility assessment it was found that, at the majority of sites, medical records are not available in electronic format and archives are not easily accessible. Sites also expressed concerns on the limitation of their medical records maintenance: data that had been generated might not be recorded or might not be retrieved. Hence a prospective study design is proposed to ease access to quality data.

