## 5.3 Secondary study outcomes

### 5.3.1 Secondary study outcome 1 – Proportion of cases classified by level

#### 5.3.1.1 Health outcomes

For each health outcome, the proportion of cases that can be classified according to each GAIA case definition level will be assessed.

*Proportion of cases identified that can be classified by level*

- For each health outcome, the proportion of cases identified that can be classified according to each GAIA case definition level will be assessed.

---

 In this document, 'classified' will mean 'classified according to the GAIA case definitions'

- The denominator will be the number of cases *identified* for one outcome; the numerator will be the number of classified cases for each level of the GAIA case definition.

*Proportion of cases classified by level*

- For each health outcome, the proportion of cases classified by level will be calculated.
- The denominator will be the number of cases *classified* for one outcome for all levels; the numerator will be the number of classified cases for each level of the GAIA case definition.

These proportions will be reported overall, and stratified by site/country/region, and by health facility level (primary/secondary/tertiary).

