## **5.4 Exploratory study outcomes**

### **5.4.1 Missing elements to meet GAIA case definition**

To better understand why GAIA case definitions are not met, the type of data elements that are required by the GAIA case definition but that are missing will be described.

For each health outcome, the reasons why identified cases could not be classified will be tabulated (e.g. four identified cases of neonatal death could not be classified because date of death was unknown).

If feasible, reasons will be grouped, and proportions will be calculated.

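### The primary applicability denominator (5.2.2.1) is conditional on CRF completion, so recruited cases without a completed CRF drop out and applicability may be overstated

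*Protocol*

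**What the plan says.** Section 5.2.2.1 introduces the primary measure as "calculating the proportion of cases identified that can be classified" under the GAIA definition. The next sentence narrows it: "The denominator will be the number of cases identified for which the CRF was completed for one health outcome". Section 4.7 attaches no CRF condition to being identified: "Identified cases are defined as children delivered at the site with a diagnosis of one of the health outcomes of interest at the same site".

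Section 4.9 describes recruitment. Once an outcome occurs, the criteria are met and consent is given, "the infant enters the study". Recruitment continues "until 100 cases for each outcome have been recruited, or the end of the study period is reached, whichever occurs first". This recruited set is defined without reference to whether a CRF is later completed.

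The by-level proportion in section 5.3.1.1 has a different base: "The denominator will be the number of cases *identified* for one outcome". On missing information, section 5.4.1 says that "the reasons why identified cases could not be classified will be tabulated" and gives unknown date of death as an example. Section 5.5 rules out imputation and speaks only of data recorded in the eCRFs. The protocol neither defines a completed CRF nor says what happens to a recruited case that lacks one.

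**The concern.** Cases are found through registries as well as medical records, while CRFs are filled in from the individual records of mother and child (both section 4.8). A case can thus appear in a delivery register while its chart is unavailable. Section 4.1 reports that sites were worried about this: "data that had been generated might not be recorded or might not be retrieved".

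The outcome is meant to show whether sites can supply what the GAIA definitions need. If a CRF is not completed because that information could not be obtained, the denominator removes a failure that the outcome should count. Results are stratified by site, country, region and facility level, so unequal completion would also distort those comparisons.

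**Working it through.** **The plan's own figure.** Table 1 (section 5.1.2) follows from n = z²p(1 − p)/d². The confidence level is not stated there; 95% is assumed, so z = 1.96. With p = 0.50 and d = 0.10, n = 96.04, rounded up to the stated 97. The other cells also reproduce, apart from rounding (384.15 is given as 384). With the target of 100 cases per outcome and site, the half-width at p = 50% is 1.96 × √(0.25/100) = 9.8 points.

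**Inputs for the bias.**
- A: applicability among cases with a completed CRF. Values of 50% and 80% are taken from Table 1; 90% is added.
- m: share of recruited cases without a completed CRF. Not given; a range of 2% to 30% is assumed.
- B: share of those cases that could nevertheless have been classified. Not given.

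**Formula.** The plan reports A. The share classifiable among all recruited cases is A(1 − m) + Bm. The overstatement is the difference, m(A − B). It is largest at B = 0, where it equals A × m, and it is zero if m = 0 or B = A.

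**Share among all recruited cases at B = 0, the worst case:**

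| Reported A | m = 2% | m = 5% | m = 10% | m = 20% | m = 30% |
|---|---|---|---|---|---|
| 50% | 49.0% | 47.5% | 45.0% | 40.0% | 35.0% |
| 80% | 78.4% | 76.0% | 72.0% | 64.0% | 56.0% |
| 90% | 88.2% | 85.5% | 81.0% | 72.0% | 63.0% |

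At A = 80% the maximum overstatement is 1.6, 8 and 16 points for m = 2%, 10% and 20%. At A = 50% and m = 20% it is 10 points, about the planned half-width of 9.8.

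**Site comparison (illustration).** Two sites each recruit 100 cases and classify 64. One completes all CRFs and reports 64/100 = 64%. The other completes 80 and reports 64/80 = 80%.

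**Mismatch with 5.3.1.1 (illustration).** Suppose 400 cases are identified, 100 are recruited with CRFs and 80 are classified. The primary proportion is 80/100 = 80%. The by-level proportions, taken over all identified cases, sum to only 80/400 = 20%. All identified cases is therefore not a usable base where the cap applies.

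**The case against.** The strongest defence is that the CRF condition may simply mark the recruited set. Cases beyond the cap or without consent never get a CRF, so some restriction is needed. If every recruited case gets a CRF, the planned and proposed denominators coincide. This is a fair reading, but the text conditions on completion, whereas section 4.9 already supplies a set that respects cap and consent without it.

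A reader might infer that applicability is shown to be biased upwards, or that sites with the worst records will report the best results. The documents do not support this. Nearly all CRF items in Annex V accept unknown as an answer, and section 5.4.1 treats a case with an unknown element as identified but not classifiable. Poor records then lower applicability, as they should. The reassurance is incomplete: completion is undefined, and a few items as shown offer no such option, for example the timing of head circumference measurement and gestational age by ultrasound.

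Three further inferences go too far:
- Section 4.1 does not call retrieval failure the sites' main problem. It reports concerns and offers the prospective design as the response. Source mapping (8.3), eCRF checks and queries (8.1) and performance reports (8.7) also help.
- Nothing says that cases without a CRF vanish from the 5.4.1 reasons. That section has no CRF restriction.
- A(1 − m) is not the true share. It assumes that no case without a CRF could be classified, yet Level 4 in Annex III accepts limited information for small for gestational age, stillbirth and microcephaly.

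It also stands that a CRF can be missing because of workload, device failure or withdrawal, which section 9.1 permits at any time. Counting these as not classified would bias the result downwards. Finally, the statistical analysis plan is not at hand and may define completion, but the denominator itself is fixed in the protocol.

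**Conclusion.** The point holds as a conditional one. Section 5.2.2.1 makes the primary denominator depend on CRF completion, which neither the cap nor consent requires, and leaves recruited cases without a completed CRF unaddressed. If non-completion is linked to records that were not made or not retrieved, applicability is overstated by at most A × m. The actual size cannot be computed because the protocol gives no m, and it is zero if every recruited case gets a CRF. The denominator mismatch between 5.2.2.1 and 5.3.1.1 does not depend on these assumptions. The change is worth making: it alters nothing if the recruited and completed sets coincide, and removes a selection effect if they differ because records are unavailable.

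**What to change.** In section 5.2.2.1:
- Use as denominator all consented cases recruited for the outcome within the 100-case cap, excluding withdrawals of consent.
- Define a completed CRF, and count a recruited case with no CRF or an incomplete one as not classified.
- Report the number of such cases and the cause per site, and list this among the 5.4.1 reasons.
- Give the proportion among completed CRFs as a sensitivity figure.

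In section 5.3.1.1, use the same recruited denominator for the proportion of identified cases classified by level, so that the levels sum to the primary figure.

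The cost is mainly wording, since recruitment and eCRF entry both run through the EDC. Annex V as shown has no item for why a CRF was not completed, so the cause may need one field or a site log. Headline proportions may be slightly lower, and CRFs missing for purely operational reasons will count against applicability. Both figures should therefore be shown side by side.

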#### 3.3 Exploratory objectives

1. To assess which missing data elements are preventing identified cases from meeting the GAIA case definition lowest level of diagnostic certainty.
2. To assess which missing data elements are preventing classified cases from meeting a better level of diagnostic certainty.

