| 
Recognised pathogena identified using a validated method and from a normally sterile siteb
 
If an organism normally considered non-pathogenic is isolated from blood culturesa: Level 1 requires its identification from at least 2 blood cultures taken from two different sites, or at 2 different times, PLUS 1 of the criteria as per level 2 of evidence
                                                                                                                                                                                                                                                                                                                                                                                                                                                                                                                                                                                                                                                                              | 
Not meeting Level 1 of evidence
 
AND
 
3 or more criteria:
 
 
• Temperature <math>\geq 37.5^{\circ}\text{C}</math> or <math>< 35.5^{\circ}\text{C}</math>f
 
• Tachycardiad or new or more frequent episodes of bradycardiad
 
• New or more frequent episodes of apnead or increased oxygen requirement or increased requirement for ventilatory support
 
• Lethargy or moving only when stimulated or hypotonia or irritability
 
• Difficulty in feeding or abdominal distention
 
• Pallor or poor perfusiond or hypotensiond
 
• Abnormal White Cell Countd or I/T ratio <math>> 0.2</math>
 
• Abnormal platelet countd
 
• Increasede inflammatory markers (CRP, procalcitonin)
 
• Metabolic acidosis as defined by a base excess (BE)d
 
 | 
Not meeting Level 1 or 2 of evidence
 
AND
 
2 or more of the following criteria:
 
 
• Temperature <math>\geq 37.5^{\circ}\text{C}</math> or <math>< 35.5^{\circ}\text{C}</math>f
 
• Tachypnead or severe chest indrawing or grunting or cyanosis
 
• Change in level of activity
 
• History of feeding difficulty
 
• History of convulsions
 
 |

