#### Level 5 of diagnostic certainty

- No evidence of SGA or a confirmed diagnosis other than SGA

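### The applicability proportion does not separate a documented non-case from a case with too little data, and the outcomes are not scored alike

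*Protocol*

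**What the plan says.** Under Protocol 4.7 a case is identified by a diagnosis made at the site; 4.8 allows this to be found by free-text search or by the ICD codes in Annex IV. Section 4.10 then assigns GAIA levels with the automated tool: "Level 1-3, and Level 4-5 when applicable".

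Section 5.2.2.1 defines applicability as a fraction. Its lower part is given in these words: "The denominator will be the number of cases identified for which the CRF was completed for one health outcome". For the upper part, the same section states that "the numerator will be the number of cases identified for that health outcome that can be classified according to the GAIA case definition". The footnote under 5.3.1.1 explains the word classified only by pointing back to the GAIA definitions, so it does not say whether a definite non-case counts.

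The exploratory part treats failure to meet a definition as a matter of missing data. Objective 1 in 3.3 reads: "To assess which missing data elements are preventing identified cases from meeting the GAIA case definition lowest level of diagnostic certainty". Section 5.4.1 sets out to explain why definitions are not met and states that "the type of data elements that are required by the GAIA case definition but that are missing will be described".

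In Annex III only SGA has a level for a non-case, Level 5: "No evidence of SGA or a confirmed diagnosis other than SGA".

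**The concern.** An identified case can fail to reach a level for two reasons. Required data may be absent, so the definition could not be applied. Or the data may be there and the criteria not met, so the definition was applied and the answer was no. Section 2.1 gives the motive for this objective: some criteria may be beyond what a site can do clinically. Only the first reason speaks to that. The second reflects how often the site's diagnosis is confirmed.

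If the two are pooled, a site that documents well but diagnoses on suspicion can look no better than a site with poor records. The chi-square comparison in 5.3.2 would then attribute to facility level, staff or equipment what is really a difference in diagnostic threshold.

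**Working it through.** **Outcome by outcome, from Annex III**

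- *Neonatal infection.* There is no non-case level. The lowest bloodstream level still needs "2 or more of the following criteria". An infant diagnosed on suspicion, with the relevant items recorded and too few present for any level, is unclassified. The Annex IV codes also include conjunctivitis and skin infection, whereas 4.7.4 limits the outcome to bloodstream infection, respiratory infection and meningitis.
- *Low birth weight.* There is no non-case level, and Levels 1 to 4 all require a weight or weight category under 2500 g. The ICD-9 list includes 765.09 and 765.19, both for 2,500 g and over.
- *SGA.* Level 5 is a non-case level and lies within the levels named in 4.10, so a refuted case can count as classified.
- *Preterm birth.* The levels list only dating methods; the 37-week limit stands in 4.7.5 and the CRF. Whether a well-dated term infant receives a level is unclear.
- *Congenital microcephaly.* Level 3B accepts one inpatient coded diagnosis, and Level 4 accepts other codes or inspection without measurement. A coded over-diagnosis is therefore still classified.
- *Neonatal death and stillbirth.* There is no non-case level, but 4.7 identifies these outcomes in nearly the same terms as Annex III, so refutation is less likely.

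**The plan's own figure.** For Table 1 (5.1.2), n = z²p(1−p)/d². With p = 0.5, d = 0.10 and an assumed two-sided 95% level (the table does not state one), 1.96² × 0.25 / 0.01 = 96.04, rounded up to 97 as printed. The other cells reproduce to rounding. At the planned 100 cases the half-width is 1.96 × √(0.25/100) = 9.8 points.

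**Effect of refuted cases.** Per N = 100 identified cases, let f be the number whose recorded data exclude every level that denotes a case, and m the number that reach no level because data are missing. The documents give neither. I assume f = 0 to 40 and m = 0 to 20.

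- As written, with no non-case level: (N − f − m)/N. This is also the confirmed share.
- Definition resolved either way: (N − m)/N. This is also the SGA result if Level 5 counts.

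| m | f | As written, no non-case level | Resolved either way (SGA with Level 5) |
|---|---|---|---|
| 0 | 10 | 90% | 100% |
| 0 | 20 | 80% | 100% |
| 0 | 40 | 60% | 100% |
| 10 | 20 | 70% | 90% |
| 20 | 0 | 80% | 80% |
| 20 | 20 | 60% | 80% |

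The second and fifth rows both report 80%, yet the definition could be applied to 100% of cases in one and 80% in the other. The fourth row gives 70% for infection and 90% for SGA from the same data profile.

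**Chi-square in 5.3.2.** Take two strata of 100 with no missing data and f = 5 against f = 20: 200 × (95 × 20 − 5 × 80)² / (100 × 100 × 175 × 25) = 10.29, p = 0.0013. With f = 10 against 20 it is 3.92, p = 0.048. In neither example do the strata differ in ability to apply the definition.

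**Case count for the odds ratio.** Section 5.2.1 uses the number of cases classified. In the SGA example with m = 10 and f = 20, 90 are classified but only 70 are SGA. The count is too high by a factor of 90/70 = 1.29, so the minimum detectable odds ratio would look better than it is.

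**The case against.** A reader might infer that every outcome except SGA is affected, that applicability is biased downward throughout, and that the bias has a known size. The documents do not support this. The Annex III text for preterm birth and microcephaly, and the way neonatal death and stillbirth are identified, leave mainly neonatal infection and, to a lesser extent, low birth weight. Nothing in the protocol gives a refuted share.

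That share may also be small. To exclude bloodstream Level 2 one must know about white cells, platelets, inflammatory markers and base excess; where these were not measured the case is undetermined, not refuted. The Annex IV codes can be read as search aids, since 4.7 still requires a diagnosis of the outcome, and an infant of 2,500 g or more may never become an identified case. All of this stands, and it limits the size.

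It is also fair that the proportion is not a pure measure of data adequacy: SGA, stillbirth and microcephaly have a Level 4 for data-poor cases, which count as classified. The level-specific tables in 5.3.1.1 show this, and the present point does not depend on it.

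Two further defences carry less weight. The classification tool may return a non-case result, and the SAP may say how to code it. But the protocol itself fixes the numerator and denominator and does not say on which side such a result falls. Section 5.4.1 does tabulate reasons for non-classification and could reveal refuted cases, but it is exploratory and leaves the primary proportion unchanged.

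**Conclusion.** The point holds in a limited form. As defined, applicability gives one score to two different findings for neonatal infection and low birth weight, and it treats SGA on the opposite footing. Preterm birth is ambiguous, and microcephaly is largely protected.

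The size is conditional: 10 points for each 10 refuted cases per 100, with 10 already matching the 9.8-point half-width at 100 cases. This is arithmetic on an assumed share, not evidence that the share is that large. The SGA consequence rests on reading Level 5 as a classification, which 4.10 allows and nothing in the protocol rules out. The plan should be changed on this point, because the present wording cannot tell the two findings apart however the data fall.

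**What to change.** In 5.2.2.1, score every identified case with a CRF, for all seven outcomes, as one of:

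- (a) meets a GAIA level that denotes a case;
- (b) enough data and criteria not met, including SGA Level 5 and, for preterm birth, a dated gestational age of 37 weeks or more;
- (c) cannot be determined.

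Use (b) only when the recorded answers exclude every level in (a), and (c) when an unknown or unmeasured item leaves one open.

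Report applicability as (a + b)/all cases with a CRF, and the confirmed share, a/all, beside it. Use the same scoring in the 5.3.2 comparison, limit the 5.4.1 missing-element tables to (c), and use only (a) for the minimum detectable risk in 5.2.1.

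No new data are needed: most infection CRF items already separate No from Unknown or not measured. The cost is an exclusion rule programmed for each outcome, which must also say how a test that was never done is treated, and one or two more rows per table.
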